## Abstract

**Introduction:**

Low back pain (LBP) is the leading global cause of disability. Patients with moderate to severe LBP who respond positively to a diagnostic medial nerve branch block can be offered radiofrequency denervation (RFD). However, high-quality evidence on the effectiveness of RFD is lacking.

**Methods and analysis:**

RADICAL (RADIofrequenCy denervAtion for Low back pain) is a double-blind, parallel-group, superiority randomised controlled trial. A total of 250 adults listed for RFD will be recruited from approximately 20 National Health Service (NHS) pain and spinal clinics. Recruitment processes will be optimised through qualitative research during a 12-month internal pilot phase. Participants will be randomised in theatre using a 1:1 allocation ratio to RFD or placebo. RFD technique will follow best practice guidelines developed for the trial. Placebo RFD will follow the same protocol, but the electrode tip temperature will not be raised. Participants who do not experience a clinically meaningful improvement in pain 3 months after randomisation will be offered the alternative intervention to the one provided at the outset without disclosing the original allocation. The primary clinical outcome will be pain severity, measured using a pain Numeric Rating Scale, at 3 months after randomisation. Secondary outcomes will be assessed up to 2 years after randomisation and include disability, health-related quality of life, psychological distress, time to pain recovery, satisfaction, adverse events, work outcomes and healthcare utilisation. The primary statistical analyses will be by intention to treat and will follow a prespecified analysis plan. The primary economic evaluation will take an NHS and social services perspective and estimate the discounted cost per quality-adjusted life-year and incremental net benefit of RFD over the 2-year follow-up period.

**Ethics and dissemination:**

Ethics approval was obtained from the London—Fulham Research Ethics Committee (21/LO/0471). Results will be disseminated in open-access publications and plain language summaries.

**Trial registration number:**

ISRCTN16473239.

STRENGTHS AND LIMITATIONS OF THIS STUDYThe trial has a pragmatic design integrated into standard care pathways.Guidelines for radiofrequency denervation (RFD) technique were developed during a national workshop with pain clinicians, ensuring that the techniques used in the trial are acceptable to clinicians and reflect best practice recommendations.A training video has been developed to support clinicians in performing the RFD technique to be used in the trial.Offering participants who do not experience an improvement in pain after 3 months the alternative intervention to which they were randomised may increase trial acceptability while maintaining blinding.There is a time lag between consent (waiting list for RFD) and randomisation (in theatre), which may impact on participant engagement.

## Introduction

 Low back pain (LBP) is the leading global cause of healthy life years lost due to disability,^1^ and between 58% and 84% of people in the UK will experience back pain in their lifetime.^2^ LBP is associated with high personal, societal and economic burden.^3^ It can impact many aspects of patients’ lives, and in some cases cause life-changing psychological and social consequences including disengagement from meaningful activities, changed identity, psychological problems, damaged relationships and inability to work.^4 5^ LBP is the most common musculoskeletal reason for general practitioner appointments, accounting for 417 consultations per year per 10 000 patients registered^6^; approximately one-third of the direct healthcare costs associated with LBP are incurred in the hospital sector.^7^

Non-surgical interventions recommended by the National Institute for Health and Care Excellence (NICE) for conservative management of LBP are self-management, exercise, psychological therapy, combined physical and psychological programmes, and non-steroidal anti-inflammatory drugs.^8^ NICE guidelines also recommend that patients with moderate to severe LBP, clinical features suggesting that a facet joint is the main source of pain and insufficient improvement in symptoms with conservative management, can be offered radiofrequency denervation (RFD) of the medial nerve to a facet joint, providing that they have a positive response to a diagnostic, local anaesthetic medial nerve branch block (MNBB). RFD is a minimally invasive outpatient procedure, where a needle is placed into the back and heated up to damage the nerve, thereby interrupting the pain signal. Approximately 13 000 RFDs of the lumbar facet joints are performed annually in the National Health Service (NHS), with a cost to the NHS of around £22 million per year.^9^

Systematic and narrative reviews of the effectiveness of RFD have been published with conflicting conclusions.^10^,^16^ A Cochrane review, published in 2015, concluded that there was no high-quality evidence that RFD provides pain relief for patients with chronic LBP.^15^ In 2017, the MINT trial (published after the systematic reviews) concluded that RFD combined with an exercise programme was not superior to an exercise programme alone.^17^ However, this trial received criticism on a number of methodological grounds, including, variation in RFD operator protocols and high numbers of patients in the control group receiving RFD.^18^,^22^ Hence, the effectiveness of RFD is uncertain due to a lack of high-quality evidence,^15^ and NICE recommends that further research is needed.^8^

The RADICAL (RADIofrequenCy denervAtion for Low back pain) trial aims to provide this evidence by comparing the effectiveness and cost-effectiveness of RFD versus placebo for chronic moderate to severe localised LBP. Specific objectives are to estimate (1) the difference between groups in pain severity 3 months after RFD; (2) differences between groups in back-specific disability, health-related quality of life (HRQoL), psychological distress, time to pain recovery, satisfaction with treatment outcome, frequency of uptake of offer of repeat RFD, adverse events, work outcomes and further healthcare use and (3) the cost-effectiveness of RFD compared with placebo.

## Methods and analysis

### Trial design

RADICAL is a multicentre, pragmatic, double-blind, parallel-group, placebo-controlled, superiority randomised controlled trial. Patients will be recruited from approximately 20 multidisciplinary pain and spinal clinics providing RFD in secondary care NHS centres (figure 1).

**Figure 1 F1:**
[figure not shown]
Trial schema. EQ-5D-5L, EuroQol 5-dimension five-level questionnaire; NRS, Numeric Rating Scale; RFD, radiofrequency denervation.

### Eligibility criteria

Patients will be eligible for the study if all the following apply:

≥18 years of age.LBP is the primary source of pain.Positive response to a single diagnostic MNBB with no steroids administered. Based on the outcome of a meeting of RADICAL clinicians,^23^ a positive response is defined as ≥60% pain relief in the first 24 hours, based on patient-reported assessment. Final eligibility will be met if a patient’s pain returns to ≥5 on a 0–10 Numeric Rating Scale (NRS) after MNBB.Chronic LBP (>3 months duration) assumed due to the fact the patient was listed for MNBB.Moderate to severe LBP (NRS score ≥5).Listed for RFD.

Patients will be excluded if any of the following apply:

Known pregnancy.Severe depression (Hospital Anxiety and Depression Scale^24^ depression score ≥15) (assessed following consent).Known previous RFD.Known previous back surgery where metal-work has been used in the lumbar spine.Pacemaker or implantable cardioverter defibrillator.Clinical suspicion that an alternative diagnosis is the reason for LBP (as defined by NICE,^8^ including, but not limited to: metastatic spinal cord compression, spinal injury, spondyloarthritis or cancer).Prisoners.Lacks capacity to consent.Existing co-enrolment in another clinical study if (1) the intervention in the other study is expected to influence the primary outcome; (2) it is considered too burdensome for the patient or (3) it is not permitted by the other study.

No restrictions will be placed on usual care, and all co-interventions are permitted to reflect usual NHS practice. Data on co-interventions will not be collected.

### Patient recruitment

Potential patients will be identified from RFD waiting lists and those potentially eligible will receive a patient information leaflet (PIL). The PIL will contain a web address where patients can access an information video to supplement the PIL. The local research team will then contact the patient to discuss the study further and answer any questions they may have. If a patient meets the initial eligibility criteria and decides to participate, the research team will request written informed consent. A copy of the informed consent form can be requested by contacting the RADICAL study team at [contact]. Eligibility for randomisation will depend on further (post-consent) eligibility checks.

Details of all patients approached and reasons for non-participation will be documented. Participants will also be given the option for their data to be stored for potential use in future research and/or training. Participants can withdraw at any time and will be treated according to standard hospital procedures. Data collected up until the point of withdrawal will be included in the analysis.

### Randomisation and blinding

Randomisation of eligible participants will be performed using a secure internet-based randomisation system, ensuring allocation concealment. Participants will be allocated in a 1:1 ratio to either RFD or placebo. A computer-generated allocation sequence will be prepared by an independent statistician, using random permuted blocks of varying size and stratified by the operator to ensure that any operator effect is distributed equally across groups.

Participants, their clinical care team and the local research team will not be informed of the allocation. Radiofrequency machines to be used in the trial will have to meet key criteria, including having an appropriate method for maintaining blinding of the clinical team and the participant. The trained randomiser will randomise the participant and then control the electrode temperature. The machine display (showing the temperature) will not be visible to the rest of the team in the theatre. This person will have no other role in the trial. Treatment allocation will only be unblinded on participant request or if clinically indicated; for example, in the event of a serious adverse event requiring knowledge of the allocation for treatment. The success of blinding will be assessed using the Bang Blinding Index.^25^

### Intervention

The intervention is RFD of the lumbar medial branches of the dorsal rami performed under local anaesthetic, with sedation if needed. Although there are international consensus practice guidelines for performing RFD,^26^ there is considerable variation in RFD technique across clinicians and centres in the UK.^27^ To refine the RFD technique for the trial, a national consensus meeting was held with clinicians, patients and academics.^23^ Components of the RFD procedure were classified as mandatory or recommended (see online supplemental file), based on existing best practice recommendations.

### Placebo

A placebo control will be used to minimise bias, which is important as the primary outcome is patient reported. The placebo treatment will follow the same RFD protocol as the intervention group, but the temperature of the electrode tip will not be raised.

### Clinical training

Clinicians who are unfamiliar with the RFD technique used within the trial will complete training prior to delivering the trial intervention. This will include an online video (https://www.youtube.com/watch?v=j4nzkdgMWgI) and/or attendance at cadaver workshops.

### Quality assurance measures

X-rays from at least three views for each lesion, from each clinician’s first case, will be shared with a clinical expert on the Trial Management Group (TMG) so that needle placement can be checked. Placement quality will be recorded and feedback will be given. If needle placement is poor, the study clinical experts will agree on a way forward, discuss with the TMG and give feedback to the clinician on a case-by-case basis. X-rays from at least three views for each lesion, for every participant procedure, will be saved locally, for potential future monitoring.

### Adverse events

Adverse events that are expected due to RFD will be recorded between randomisation and 2 weeks post-randomisation. Serious adverse events will be recorded between randomisation and the 2-year follow-up. Between randomisation and 6 months post-randomisation, all unexpected or fatal serious adverse events will be reported to the sponsor.

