### Outcomes

The primary outcome is LBP severity (average intensity of LBP over the past week, assessed using the 0–10 NRS) at 3 months post-randomisation. Secondary outcomes will be collected up to 2 years after randomisation and include:

Functional disability is measured using the Oswestry Disability Index^28^ version 2.1b.HRQoL was measured using the EuroQol 5-dimension five-level questionnaire (EQ-5D-5L).^29^General health is measured using the 12-Item Short Form Survey (SF-12) Physical Component Score.^30^Mental health is measured using the SF-12 Mental Component Score.Time to pain recovery: time from randomisation until the participant first reports a pain reduction of ≥60% that remains at ≥60% lower than baseline at their next assessment.Uptake of offer of alternative treatment (ie, blinded cross-over to RFD/placebo) after 3 months.Satisfaction with treatment outcome using a Likert scale.Adverse health events.Work outcomes were assessed using the Work Productivity and Activity Impairment (WPAI) questionnaire.^31^Resource use assessed via a patient-reported resource use questionnaire.

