### Data collection

Screening data will be collected before consent to establish patient eligibility. Some demographic data (see online supplemental file), information about pain severity and duration of current LBP episode will also be collected from participants and non-participants, as far as possible, at the time of screening, to characterise the population and to interpret the applicability of the trial findings to the reference population. The schedule of data collection outlined in online supplemental table 1 will take place after consent has been received. Data will either be collected on paper data collection forms and entered into the study database or entered directly into the database. Data for the primary outcome and most secondary outcomes will be collected via patient-completed questionnaires. Participants will be followed up at 2, 4, 6, 8 and 10 weeks for pain severity, as well as HRQoL at 6 weeks and adverse health events at 2 and 6 weeks. After this, participants will complete postal/online questionnaires at 3, 6, 12, 18 and 24 months. The participant’s time in the study will end after they have completed the follow-up at 24 months post-randomisation. The end of the study as a whole will be after all participants have completed the follow-up, all data queries have been resolved, the database locked and the analysis completed.

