## Discussion

Findings from the RADICAL trial will contribute to shaping clinical guidelines and service provision for patients living with chronic LBP. Study training resources, developed in line with the consensus-based best practice guidelines for RFD produced by the RADICAL team,^23^ have been positively received and taken up by clinicians across the country, demonstrating that the trial is already impacting on RFD provision by improving standards. The study opened to recruitment on 27 May 2022 and is currently recruiting across 17 centres. As of 8 February 2024, 83 patients have been recruited and 47 randomised. The original study end date was 31 December 2024. An extension until 31 July 2026 is currently being requested to complete the study.

During the internal pilot phase, RADICAL experienced three substantial challenges to delivery: delays in site opening, complex screening processes limiting site capacity to recruit patients and long NHS waiting times for RFD. Opening sites has been an ongoing issue due to the continuing impact of the COVID-19 pandemic on research infrastructure; we have experienced delays of up to 2 years from feasibility assessment to site opening due to research and development departments’ limited capacity to process local approvals. However, we have recently seen an improvement in site opening timelines, with a recent site opening in 4 months. Identification of sites with the necessary clinical expertise and engagement, alongside the research infrastructure to deliver the trial, has been key, and we have achieved this through a combination of national calls for sites through the National Institute for Health Research Clinical Research Network and one-to-one discussions with clinicians.

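### Expected-event recording and sponsor reporting of serious events are timed from randomisation only, so the second blinded procedure, offered from 3 months, has no expected-event window and at most partial sponsor-reporting cover

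*Protocol article*

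**What the plan says.** The Adverse events section of the protocol article sets three windows, all starting at randomisation:

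- Expected events: "Adverse events that are expected due to RFD will be recorded between randomisation and 2 weeks post-randomisation".
- Recording of SAEs: "Serious adverse events will be recorded between randomisation and the 2-year follow-up".
- Reporting to the sponsor: "Between randomisation and 6 months post-randomisation, all unexpected or fatal serious adverse events will be reported to the sponsor".

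Participants are randomised in theatre, so randomisation and the first procedure coincide in practice.

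The Abstract adds a second procedure: "Participants who do not experience a clinically meaningful improvement in pain 3 months after randomisation will be offered the alternative intervention". The Outcomes section lists it as a secondary outcome: "Uptake of offer of alternative treatment (ie, blinded cross-over to RFD/placebo) after 3 months". The Discussion describes the same offer as a design feature meant to help recruitment.

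Data collection names two early contacts for "adverse health events at 2 and 6 weeks". Outcomes lists adverse health events among the secondary outcomes, under the general statement "Secondary outcomes will be collected up to 2 years after randomisation". No section of the article restarts an adverse-event window at the second procedure or names an adverse-event contact tied to it.

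**The concern.** Timing from randomisation works when there is one procedure per participant. Here the design itself provides for a second one, and for those first given placebo it is the first time the electrode is heated. Participants first given RFD have a further needle procedure. A window that has closed before the earliest possible second procedure cannot record its expected effects.

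Three things are at stake. First, adverse events are a named objective and secondary outcome, and the harms data would describe only first procedures. Second, an unexpected or fatal SAE after a late second procedure could fall outside the stated period for reporting to the sponsor. Third, SAEs after crossover RFD would be counted under placebo if they were summarised by randomised arm alone. Statistical analyses says only that frequencies of adverse events will be described. The switching-adjusted exploratory analyses in that section do not mention safety.

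**Working it through.** The plan gives no figure to reproduce here. The check is calendar arithmetic on the stated windows.

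**Inputs**

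- Expected-event window: 0 to 2 weeks (Adverse events).
- Sponsor reporting of unexpected or fatal SAEs: 0 to 6 months (Adverse events).
- SAE recording: 0 to 24 months (Adverse events).
- Named adverse-event contacts: 2 and 6 weeks (Data collection).
- Earliest second procedure: 3 months (Abstract; Outcomes).
- Delay from the 3-month offer to the second procedure, *d* months: not stated, so taken as an assumption from 0 to 18.

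**Step 1: expected events.** Three months is 3 × 52.18/12 ≈ 13.0 weeks.

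- Gap after the 2-week window closes: 13.0 − 2 = 11.0 weeks at the least.
- Gap after the 6-week contact: 13.0 − 6 = 7.0 weeks at the least.

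Both gaps grow with *d*. This result needs no assumption about delay or uptake.

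**Step 2: sponsor reporting and SAE recording.** The second procedure takes place at month 3 + *d*.

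- Sponsor-reporting time left = max(0, 6 − (3 + *d*)) = max(0, 3 − *d*).
- SAE-recording time left = 24 − (3 + *d*) = 21 − *d*.

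| Assumed delay *d* (months) | Second procedure at month | Sponsor reporting left (months) | SAE recording left (months) |
|---|---|---|---|
| 0 | 3 | 3 | 21 |
| 1 | 4 | 2 | 20 |
| 2 | 5 | 1 | 19 |
| 2.5 | 5.5 | 0.5 | 18.5 |
| 3 | 6 | 0 | 18 |
| 6 | 9 | 0 | 15 |
| 18 | 21 | 0 | 3 |

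Even with no delay, sponsor reporting after the second procedure lasts half as long as after the first (3 months against 6). It reaches zero at *d* = 3. SAE recording still covers the second procedure throughout the range.

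**Step 3: an illustration of scale.** Uptake is not given. Suppose a fraction *x* of the 125 placebo participants accepts, with no attrition and all 125 in the RFD arm treated. The share of active procedures without expected-event recording is then 125*x* / (125 + 125*x*) = *x* / (1 + *x*):

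| Assumed uptake *x* | Crossover RFDs | Share of all active RFDs |
|---|---|---|
| 0.30 | 37.5 (about 38) | 23% |
| 0.40 | 50 | 29% |
| 0.50 | 62.5 (about 63) | 33% |
| 0.60 | 75 | 38% |

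Lower uptake shrinks the share but does not close the gap.

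**Step 4: which comparison is affected.** The 2-week window closes about 11 weeks before any crossover, so the expected-event comparison for the first procedure is RFD against placebo as randomised. Only SAEs after crossover raise a question of attribution.

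**The case against.** The strongest objection is that this is a condensed article. Data collection refers the schedule to a supplemental table, and protocol version 5.0 is in use; neither is shown. Either may set a window after reintervention. That stands as a reason for lower confidence and severity. It does not remove the point, because the article states its windows positively and gives each the same starting event. If the full protocol restarts them, the article misdescribes the trial.

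Several stronger readings are tempting, and the document does not support them:

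- **Serious harms after the second procedure are lost.** They are not, because SAE recording runs to 2 years. The recording gap concerns expected events, and the trial also has a Data Monitoring and Safety Committee.
- **Many second procedures fall after 6 months.** The Discussion does report "long NHS waiting times for RFD", and the pilot criteria allow a 3-month lag between consent and randomisation; a similar lag would put the second procedure at month 6. But nothing says that reintervention joins the same waiting list. The lag of 18 months or more in the Discussion belonged to a superseded pathway that included the wait for the diagnostic block. A second procedure after month 6 is possible; how often it would occur cannot be inferred.
- **Crossover dilutes the safety comparison.** Not for expected events after the first procedure (step 4). For SAEs it depends on a table layout that the article does not give and that an analysis plan would normally set.
- **The 2-week window contradicts the 2- and 6-week contacts.** The window applies to expected events. Data collection uses the broader term adverse health events, which may include SAEs, so the two sections can be read together.
- **23–38% measures missed harm.** It is a share of procedures under an assumed uptake with no source in the document. It measures neither serious harm nor bias.

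**Conclusion.** The point holds, within limits. As the article is written, no expected event after a second trial procedure falls within the recording window, and the shortfall of at least about 11 weeks is certain. Sponsor reporting of unexpected or fatal SAEs covers at most 3 months after that procedure, and none if it takes place more than 3 months after the offer; this part depends on an unstated delay.

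The primary outcome at 3 months precedes the reintervention, so the primary estimate and power are untouched. The consequence is incomplete harms data on a named secondary outcome, possible gaps in sponsor reporting, and an open question about attributing SAEs after crossover. It deserves correction but is not of the highest severity. Confidence is moderate, because the full protocol and supplemental schedule are not shown.

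**What to change.** Reconcile the Adverse events section with the reintervention design, so that the expected-event recording window and the sponsor-reporting window are also defined relative to the second trial procedure. The length of those windows is for the sponsor to set. State that adverse events will be described by the procedure actually received as well as by randomised arm, so that SAEs after crossover RFD do not appear only under placebo.

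The cost is a protocol amendment and one short contact for each participant who has a second procedure. It can still be worthwhile: at the article's last count, 47 of the planned 250 had been randomised, leaving 250 − 47 = 203 to come. If the full protocol already contains these provisions, only the article's statement needs correcting.
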